## Abstract

**Background:**

Multilevel spinal fusion surgery has typically been associated with significant blood loss. To limit both the need for transfusions and co-morbidities associated with blood loss, the use of anti-fibrinolytic agents has been proposed. While there is some literature comparing the effectiveness of tranexamic acid (TXA) to epsilon aminocaproic acid (EACA) in cardiac procedures, there is currently no literature directly comparing TXA to EACA in orthopedic surgery.

**Methods/Design:**

Here we propose a prospective, randomized, double-blinded control study evaluating the effects of TXA, EACA, and placebo for treatment of adolescent idiopathic scoliosis (AIS), neuromuscular scoliosis (NMS), and adult deformity (AD) via corrective spinal surgery. Efficacy will be determined by intraoperative and postoperative blood loss. Other clinical outcomes that will be compared include transfusion rates, preoperative and postoperative hemodynamic values, and length of hospital stay after the procedure.

**Discussion:**

The primary goal of the study is to determine perioperative blood loss as a measure of the efficacy of TXA, EACA, and placebo. Based on current literature and the mechanism by which the medications act, we hypothesize that TXA will be more effective at reducing blood loss than EACA or placebo and result in improved patient outcomes.

**Trial Registration:**

ClinicalTrials.gov ID: NCT00958581

## Background

Multilevel spinal fusion surgery has typically been associated with significant blood loss and transfusion requirements. Significant patient factors affecting operative blood loss include duration of exposure, severity and type of spinal deformity, and patient height [1-3]. Surgery dependent factors include operating time, procedure performed, combined anterior/posterior approaches, number of vertebrae fused, number of anchors placed, average mean arterial pressure (MAP) during surgery, blood salvage techniques, and the use of anti-fibrinolytic medications [4]. Factors with an unclear role include, but are not limited to: pre-operative hemoglobin, autologous donation, history of coagulopathy, prior use of anticoagulant medication, and type of fibrinolytic medication used in the operating room.

Large quantities of intra-operative and postoperative blood loss require blood transfusion to maintain tissue perfusion and prevent end-organ damage. The use of allogenic blood, however, confers an additional risk for blood borne pathogens. Also noteworthy is the risk for transfusion related reactions, immune suppression, and a decrease in coagulation factors. There is also evidence that transfusion of allogenic blood is increasingly harmful as more blood is transfused [5]. While the innovation of autologous transfusion, cell-salvage, and pre-operative erythropoietin administration has reduced the need for allogenic transfusion, patients undergoing spinal fusion may lose up to their entire blood volume or more for highly complex spinal reconstructive procedures [6].

More recently the use of anti-fibrinolytics has come into favor for cardiac and orthopedic surgery where blood loss is of significant concern. These include aprotinin, tranexamic acid (TXA), and epsilon aminocaproic acid (EACA, trade name Amicar?). Aprotinin is a serine protease inhibitor with anti-fibrinolytic properties. In contrast, TXA and EACA are synthetic lysine analogs that act as inhibitors of fibrinolysis. TXA is ten times more potent than EACA and binds more strongly to the plasminogen molecule [7].

The safety of these treatments has been studied in the orthopedic and cardiac literature [8]. Aprotinin lost FDA approval due to safety concerns [9]. However, both TXA and EACA have excellent safety profiles and continue to be used widely by many institutions. In the spine literature, there continues to be a paucity of data evaluating the optimal guidelines or indications for administration of TXA and EACA. No studies offer level-1 evidence comparing the efficacy of both treatment options head-to-head.

## Methods/Design

### Trial Organization

This trial will be conducted at single institution, New York University-Langone Medical Center.

### Investigators

All patients are recruited through both the private offices of the investigators and clinic of New York University - Hospital for Joint Diseases. Patients are consented by the investigators, persons completing research fellowships in orthopaedic surgery and/or persons working exclusively on clinical orthopaedic research projects. These researchers all have experience seeing and consenting patients.

### Medication Supply and Randomization

On the day of surgery, the anesthesiologist orders either TXA or EACA from the pharmacy. Orders for both medications are placed onto a single order form with both the medical registration number and the patient's de-identified identification number (ID). Prior to study, patient de-identified ID numbers were randomly assigned to the TXA, EACA, or placebo (1 to 150) using computer generated random assignment. Since additional patients with neuromuscular scoliosis (NMS) and adult deformity (AD) were later included into the study, supplementary de-identified ID numbers were added to the original 150 consecutive de-identified ID numbers. In a similar fashion, these consecutive de-identified ID numbers (151 to 390) were randomly assigned to TXA, EACA or control. The updated list of de-identified ID numbers and their respective treatment groups (TXA, EACA, or Control) were also placed in a sealed envelope and made available to the physicians, anesthesiologists, and residents involved with patient care. A copy was also given to the pharmacy department and to the researchers in a sealed envelope. The list of de-identified ID numbers and their treatment groups will remain unchanged for the duration of the study. Based upon the identification number and the randomization list, the pharmacist prepares TXA, EACA, or placebo using the methods listed in this protocol.

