### Physician Blinding

While clinicians are blinded to the patient's particular treatment group, at any time during surgery or in the post-operative period any clinician can be "unblinded" to the patient's treatment group if there is a concern for a complication. In addition, all patients are followed daily by the residents and fellows on the spine service and will also be followed by spine research fellows caring for the patient. The research residents also record and document basic metabolic profile (BMP) and complete blood count (CBC) lab values daily. The research fellows pay careful attention to the blood creatinine and blood urea nitrogen/creatinine ratio (BUN/Cr) monitoring daily for possible renal failure. Sequential compression devices (SCD) are given to all spine patients and they are encouraged to mobilize out of the hospital bed on post-op day 2. Spine patients are closely monitored for signs of a DVT by the medicine attending physicians and nurses caring for patients.

The anesthesiologist, surgeon, and researcher can be unblinded from the study at any time in the case of an apparent or suspected medical emergency. A copy of the consent form is placed in every chart in addition to a list of contact numbers of research persons involved with the study. There is also a note on the front cover of the chart informing all nurses and physicians that the patient is enrolled in the study with contact information for the research fellows and for the pharmacy department. The pharmacy is instructed to release the treatment group for any patient if requested by medical personnel caring for the patient or a spine research fellow. Order forms given to the pharmacy will be kept in a secure binder and will be made available upon request. As an additional resource, all physicians, anesthesiologists, and residents involved with patient care will have access to a sealed envelope with patient de-identified ID numbers and their assigned treatment groups.

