**NMS**	
Inclusion	Exclusion
1. Between 10 and 80 years of age	1. Congenital and syndromic scoliosis
	2. Previous corrective spinal surgery that is being revised

The maximum total number of patients enrolled will be 150 of AIS (50 in each treatment arm), 90 for NMS (30 in each treatment arm), 150 for AD (50 in each treatment arm). These numbers were estimated by critically reviewing the existing spine and cardiac literature comparing TXA and EACA against placebo [6-20]. A power analysis was conducted using the literature to determine the number of patients necessary to attain significant results (Tables 2 and 3).

**Table 2 T2:** Power study to determine number of patients needed in AIS group.

	TXA		Amicar		Control		
	**Blood loss**	**Standard Deviation**	**Blood Loss**	**Standard Deviation**	**Blood Loss**	**Standard Deviation**	**Sample Size Needed**

Intra-op blood loss	1072 mL	+/- 425 mL	-	-	1420 mL	+/- 644 mL	58

Intra-op blood loss	1072 mL	+/- 425 mL	893 mL	+/- 220 mL	-	-	80

Total blood transfused	1253 mL	+/- 884 mL	-	-	1784 mL	+/- 733 mL	55

Total units transferred	-	-	1.2 U	+/- 1.1 U	2.2 U	+/- 1.3 U	34

**Table 3 T3:** Power study to determine number of patients needed for NMS group

	TXA		Amicar		Control		
	**Blood loss**	**Standard Deviation**	**Blood Loss**	**Standard Deviation**	**Blood Loss**	**Standard Deviation**	**Sample Size Needed**

Intra-op blood loss	1408 mL	+/- 605 mL	-	-	2690 mL	+/- 1266 mL	14

Intra-op blood loss	1976 mL	+/- 860 mL	1117 mL	+/- 718 mL	-	-	30

Total blood transfused	808 mL	+/- 531 mL	-	-	1391 mL	+/- 723 mL	34

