### Study Design

The study is designed as a prospective, randomized, double-blinded control trial. The patient, researcher, surgeon, and anesthesiologist will all be blinded to the patient's treatment. Patients will either receive TXA, EACA, or normal saline. The study will determine and compare differences in blood loss intra-operatively and estimate blood loss postoperatively through monitoring of subfascial Hemovac drain outputs at the incision site between the three groups. Postoperatively, laboratory values, drain outputs, and clinical outcomes will be carefully followed.

The primary goal of this study is to compare the efficacy of TXA to EACA to placebo in patients undergoing corrective spinal surgery for adolescent idiopathic scoliosis (AIS), neuromuscular scoliosis (NMS), and with adult deformity (AD). Outcome measures will include intra-operative and perioperative blood loss, transfusion rates, complete blood counts, and coagulation profiles, as well as postoperative wound drainage, complications, and length of stay.

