## Discussion

Overall, orthopedic studies have demonstrated the efficacy of TXA and EACA over placebo in relation to blood loss [8-16]. However, the specifics of this demonstrated benefit are lacking. In particular, a reduction in intra-operative blood loss has been inconsistently reported. In two recent Cochrane reviews, TXA was noted to be more efficacious than EACA at reducing total blood loss, but neither drug significantly reduced intra-operative bleeding [7,8]. The most recent review demonstrated a reduction in transfusion volume with antifibrinolytic medications in scoliosis surgery, but could not comment on the benefit of one medication over another [7,8]. In addition, studies solely reporting intra-operative blood losses may have overlooked postoperative benefits. The authors concluded that antifibrinolytic treatments have greatest efficacy in controlling postoperative bleeding, but also that more investigation was needed. Comparing trials in all surgical fields including cardiac surgery, TXA - but not EACA - was found to reduce the transfusion rate over placebo.

The cardiac literature has produced seven prospective studies comparing TXA and EACA head-to-head, but no trial was assessed as having proper patient randomization and physician blinding [7,18-20]. Moreover, for five of the seven trials the method of randomization raised uncertainty for the reviewers [7]. In addition, the trials were inappropriately powered to detect differences between TXA and EACA and excluded high-risk patients to accentuate differences between the two drugs.

The role of anti-fibrinolytics to manage blood loss, therefore, remains largely surgeon dependent and is not the standard of care in spinal deformity surgery. Of the scoliosis studies examined in the Cochrane review, only two studies adequately randomized patients and blinded both the surgeon and anesthesiologist to the patient's treatment [8]. Since operative blood loss is partly dependent upon surgical and anesthetic conditions, proper physician blinding is imperative. As stated, no single orthopedic study has prospectively compared the relative efficacy of TXA and EACA head-to-head.

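### The whole allocation list sits in a sealed envelope open to staff who are meant to be blinded, so opening it for one patient can disclose every other allocation

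*Protocol article*

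**What the plan says.** The Medication Supply and Randomization section describes two stages of allocation. First, IDs were "randomly assigned to the TXA, EACA, or placebo (1 to 150) using computer generated random assignment". After neuromuscular scoliosis and adult deformity were added, "these consecutive de-identified ID numbers (151 to 390) were randomly assigned to TXA, EACA or control". The updated ID numbers and their groups "were also placed in a sealed envelope and made available to the physicians, anesthesiologists, and residents involved with patient care". The next sentence adds: "A copy was also given to the pharmacy department and to the researchers in a sealed envelope". The section then says that the list will not be altered while the study runs.

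The Physician Blinding section repeats that physicians, anesthesiologists and residents can reach a sealed envelope holding IDs and groups, and presents it as a supplement to the pharmacy. The pharmacy itself is "instructed to release the treatment group for any patient if requested by medical personnel caring for the patient or a spine research fellow".

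Against this, the Study Design section states: "The patient, researcher, surgeon, and anesthesiologist will all be blinded". The Discussion argues that, because operative blood loss depends partly on surgical and anesthetic conditions, "proper physician blinding is imperative".

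**The concern.** An emergency code break should reveal one patient's arm to the person who needs it. Here the break available to the clinical team is the full list. A reader who opens it for one patient also sees the arms of patients already treated and of IDs not yet used, and the list is not changed afterwards.

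Two protections could be lost:

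- **Blinding.** The Statistical considerations section has blood loss estimated in the operating room, and transfusion is a compared outcome that depends on clinicians' decisions. Both can be influenced by knowing the arm.
- **Allocation concealment.** The Investigators section has consent taken by investigators, research fellows and clinical research staff, and the researchers have a copy of the list. Someone who knows the coming arms could influence who is enrolled, or when. No later analysis can repair that.

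De-identified IDs give little cover. The pharmacy order form carries both the medical registration number and the study ID, so staff who see the form can match a line on the list to a patient.

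**Working it through.** **1. Length of the list.** Inputs are the two ID ranges in Medication Supply and Randomization and the enrolment maximum under Patient selection, given as "150 of AIS (50 in each treatment arm), 90 for NMS (30 in each treatment arm), 150 for AD (50 in each treatment arm".

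- From the ID ranges: 150 + (390 − 151 + 1) = 150 + 240 = 390.
- From planned enrolment: 150 + 90 + 150 = 390.

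The two agree, so the list has one ID for each planned patient.

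**2. What one opening discloses.** If the envelope covers all 390 IDs and is opened for the k-th patient, the reader can learn k − 1 earlier arms and 390 − k unused ones, 389 in all besides the patient concerned.

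| Opened at patient | Earlier patients | Unused IDs | Unused as share of 390 |
|---|---|---|---|
| 20 | 19 | 370 | 95% |
| 60 | 59 | 330 | 85% |
| 100 | 99 | 290 | 74% |
| 200 | 199 | 190 | 49% |

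Full coverage is a reading, not an explicit statement: the supplementary IDs were added to the first 150 and the result is called the updated list. If the envelope held only the supplementary IDs, an opening would still show 240 − 1 = 239 others.

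**3. Whether the next allocation is foreseeable.** The number of unused IDs does not depend on the order in which they are issued. Knowing the arm of the very next patient does. The article calls the IDs consecutive but does not say how they are given to patients, or how they are divided among the three diagnoses. If they are issued in numerical order, overall or within a diagnosis, the next arm can be read off the list.

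**4. Who has access and who should be blinded.**

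| Role | Blinded under Study Design | Access to the list |
|---|---|---|
| Surgeon | yes | envelope made available (as treating physician) |
| Anesthesiologist | yes | envelope made available |
| Researcher | yes | copy given in a sealed envelope |
| Pharmacy | not listed | copy given; needed to prepare the drug |

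Only the pharmacy needs the list to do its work.

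**5. Conditions for unblinding.** The Physician Blinding section words these in three ways: any clinician who is worried about a complication; anesthesiologist, surgeon or researcher in an actual or suspected emergency; and pharmacy release on request by treating staff or a spine research fellow, with no condition in that sentence.

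**6. After the fix.** A single-patient code break discloses 1 allocation, instead of up to 390 including the patient concerned.

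**The case against.** The strongest reply is that an emergency need not touch the envelope. Every chart cover carries contact details for the pharmacy, which can release one patient's group; the envelope is secondary. That stands, and it makes an opening less likely. It does not remove the risk, because the envelope is still offered as a parallel route. It also shows that the envelope could be withdrawn while the pharmacy route remains.

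Other points limit what can be claimed:

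- A reader might infer that every clinician holds a copy. The text says only that clinicians have access; copies are given to the pharmacy and the researchers.
- A reader might infer that one opening ends the double blind. It unblinds whoever reads the list; patients and other staff can remain blinded.
- It is tempting to quote a probability that the list stays sealed. No opening rate can be taken from the document, and any such figure would only reflect the rate assumed.
- The pharmacy sentence follows one about emergencies in the same paragraph, so its lack of a condition may be loose wording and not a deliberate third rule. It still needs to be made clear.
- Blood loss will also be calculated from body mass, hematocrit and fluid balance, and drain output is measured. These depend less on judgement than the operating-room estimate. Transfusion decisions remain exposed.

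It may also be said that an article condenses the full protocol. But the content of the envelope and who can reach it are stated here, and access is described twice. This is a stated arrangement, not an omitted detail.

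**Conclusion.** The point holds as a flaw in the stated design. A fixed list of allocations, read as all 390, can be reached by the clinicians and researchers whom the same article declares blinded. One opening can disclose up to 389 other arms to whoever reads it; at patient 60, 330 of them would belong to IDs not yet used. Blinding and allocation concealment are therefore both at risk.

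The size rests on the envelope covering IDs 1 to 390 and on enrolment reaching the stated maximum. Prediction of the next patient's arm rests further on IDs being issued in order, which is not stated. The document does not support saying that the blind will be lost, or how likely an opening is. The case for change rests on how much a single opening would disclose.

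**What to change.** 1. Withdraw the whole-list envelopes from clinicians and researchers, and keep the list in the pharmacy only.
2. Break the code one patient at a time, through the existing pharmacy release or one opaque sealed envelope per patient.
3. Log each release.
4. Reconcile the three descriptions in the Physician Blinding section of when and to whom a code may be released, including release to a research fellow, with each other and with the Study Design statement on blinding. Which condition should apply is for the investigators to settle.

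Do not try to repair the problem with an analysis that leaves out unblinded patients. That would select on complications arising after randomization, and it would not help once the whole list had been read.

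The cost is small: a protocol amendment, recall of the envelopes and, if chosen, preparation of per-patient code breaks. The research fellows are named as chart contacts, so the amendment should say how a request that reaches them is passed on.

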### Physician Blinding

While clinicians are blinded to the patient's particular treatment group, at any time during surgery or in the post-operative period any clinician can be "unblinded" to the patient's treatment group if there is a concern for a complication. In addition, all patients are followed daily by the residents and fellows on the spine service and will also be followed by spine research fellows caring for the patient. The research residents also record and document basic metabolic profile (BMP) and complete blood count (CBC) lab values daily. The research fellows pay careful attention to the blood creatinine and blood urea nitrogen/creatinine ratio (BUN/Cr) monitoring daily for possible renal failure. Sequential compression devices (SCD) are given to all spine patients and they are encouraged to mobilize out of the hospital bed on post-op day 2. Spine patients are closely monitored for signs of a DVT by the medicine attending physicians and nurses caring for patients.

The anesthesiologist, surgeon, and researcher can be unblinded from the study at any time in the case of an apparent or suspected medical emergency. A copy of the consent form is placed in every chart in addition to a list of contact numbers of research persons involved with the study. There is also a note on the front cover of the chart informing all nurses and physicians that the patient is enrolled in the study with contact information for the research fellows and for the pharmacy department. The pharmacy is instructed to release the treatment group for any patient if requested by medical personnel caring for the patient or a spine research fellow. Order forms given to the pharmacy will be kept in a secure binder and will be made available upon request. As an additional resource, all physicians, anesthesiologists, and residents involved with patient care will have access to a sealed envelope with patient de-identified ID numbers and their assigned treatment groups.

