### Adverse events management

Complications include but are not limited to: suspected medication or allergic reaction, suspected myocardial infarction, stroke, deep vein thrombosis, pulmonary embolism, and renal failure. Other side effects that have been reported have been minor including headache, upset stomach, flushing, and hypotension. To date there has been no clear association between the use of anti-fibrinolytics, such as TXA and EACA, and renal failure or thrombosis [7,8]. A similar medication with anti-fibrinolytic properties, aprotinin, did lose FDA approval over concerns regarding renal failure in cardiac patients and the theoretical risk of thrombosis [9]. Aprotinin functions as a serine protease inhibitor. In contrast, TXA and EACA are synthetic lysine analogs that bind to and produce a structural change in plasminogen preventing conversion of plasminogen to plasmin and conversion of fibrinogen to fibrin. TXA and EACA therefore have a dual mechanism of anticoagulation: decreased fibrinolysis and decreased platelet aggregation due to the inactivation of plasmin. This difference in mechanism most likely accounts for the lack of association between the use of anti-fibrinolytics and renal failure [7,8]. Regardless, patients in the study are carefully monitored for signs of renal failure post-operatively. Any patient with an elevated or rising creatinine is carefully followed by resident and attending orthopaedic surgeons, internal medicine physicians, and the research fellows. If the elevation in creatinine is suspicious for renal failure, patients will be "unblinded" and treated appropriately. TXA and EACA have been used most in cardiac and spinal surgery and meta-analysis has clearly shown a reduction of intra-operative blood loss and allogenic transfusion rate with these medications [6-8,10,11,13].

Considering the reported reduction in operative blood loss and allogenic transfusion rate in both the cardiac and spine literature, the benefits of treatment outweigh the potential side effects. While these medications are widely used, they are currently not the standard of care in spinal surgery. This study aims to delineate the benefits of TXA versus EACA in spinal surgery, which may help to identify the patients most in need of this treatment. Complications will be diligently recorded and reported in the final manuscript.

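### The pharmacy may release a patient's arm to a spine research fellow on request alone, so complications can be classified with the arm known by people the protocol calls blinded

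*Protocol article*

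**What the plan says.** Study Design in the protocol article sets the blinding: "The patient, researcher, surgeon, and anesthesiologist will all be blinded to the patient's treatment". The same section lists complications among the outcome measures, together with wound drainage and length of stay.

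Physician Blinding gives the exceptions. Any clinician may be unblinded "if there is a concern for a complication". For a named group, which includes the researcher, the condition is different: "The anesthesiologist, surgeon, and researcher can be unblinded from the study at any time in the case of an apparent or suspected medical emergency". Later in the same paragraph comes the working instruction: "The pharmacy is instructed to release the treatment group for any patient if requested by medical personnel caring for the patient or a spine research" (meaning a fellow).

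Adverse events management adds a rule for one event: "If the elevation in creatinine is suspicious for renal failure, patients will be" unblinded and then treated. It also lists what counts as a complication: "Complications include but are not limited to: suspected medication or allergic reaction, suspected myocardial infarction, stroke, deep vein thrombosis, pulmonary embolism, and renal failure".

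Medication Supply and Randomization says that the researchers, as well as the pharmacy and the treating staff, hold the allocation list in a sealed envelope.

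**The concern.** Emergency code-breaking for treating staff is normal and is not at issue. The difficulty is that the working instruction to the pharmacy is looser than the rule it is meant to serve, and that one of the people who may use it has a part in collecting outcomes.

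If someone who judges or records a suspected event already knows the arm, that knowledge can affect how far the event is worked up and what it is finally called. Unblinding would be concentrated in patients with suspected harm, so any influence would fall first on the safety comparison of active drug with saline. Drain output, transfusion and length of stay recorded afterwards for those patients could also be collected with the arm known. The article's own Discussion stresses proper blinding and faults earlier trials for lacking it.

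**Working it through.** The document gives no figure to reproduce. The check sets the passages side by side.

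1. **Conditions for release.** Physician Blinding has three: concern about a complication (any clinician, permitted); an emergency, evident or suspected (anesthesiologist, surgeon and researcher, permitted); and a request (treating personnel or a spine research fellow, with no further condition in that sentence). Adverse events management adds a fourth: a suspicious creatinine rise, where unblinding is mandatory.

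2. **Conflict for the researcher.** The emergency sentence restricts the researcher. The pharmacy sentence does not restrict the research fellow, and it lists the fellow separately from the personnel caring for the patient. Read as written, the fellow's access does not depend on clinical need. A pharmacist following that sentence would release the code where the emergency sentence would not.

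3. **Are fellows researchers who record outcomes?** Investigators counts people completing orthopaedic research fellowships among the researchers. Physician Blinding has the fellows check creatinine and the BUN/creatinine ratio daily for possible renal failure. Investigation schedule and follow-up has the researchers fill in the data sheets. Together these make it likely that fellows record outcomes, but this is an inference. Daily laboratory values are recorded by research residents, and signs of deep vein thrombosis are watched by medicine attending physicians and nurses.

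4. **Can the arm be known before classification?** For suspected renal failure, probably yes: suspicion alone triggers a mandatory unblinding, and the fellows are among those following the creatinine. For other complications it is possible, because unblinding is permitted. No section says who classifies complications or at what point.

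5. **Size.** Let the same fraction s of each arm have a suspected event with no true drug effect, and let k1 (active) and k0 (saline) be the shares kept as complications once the code is known. The recorded relative risk is (s × k1)/(s × k0) = k1/k0. The document gives neither k1 nor k0. Assumed values show only how the result moves:
   - k1 = 0.8, k0 = 0.5: 0.8/0.5 = 1.6. With an assumed s = 6%, the rates are 0.06 × 0.8 = 4.8% and 0.06 × 0.5 = 3.0%. With 50 + 30 + 50 = 130 patients per arm (the maxima in Patient selection), that is about 6 against 4 patients.
   - k1 = 0.7, k0 = 0.6: 0.7/0.6 = 1.17.
   - k1 = k0: 1.0, no bias.

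   Events listed in Adverse events management as merely suspected (drug or allergic reaction, myocardial infarction) seem to count on suspicion alone. For these k1 = k0 = 1 and this route is closed, although whether a suspicion is raised or written down could still be affected once the arm is known.

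**The case against.** The pharmacy sentence comes after the emergency sentence in the same paragraph and can be read as its mechanics: when the emergency rule is met, the pharmacy answers the call. Fellows are also described as caring for patients, and their contact details are on the chart cover, so they have a place in the code-break route. The renal clause goes on to treatment, which shows that it is about care and not about labelling outcomes. Blinding with an emergency exception is ordinary. Release logs and blinded adjudication may be in the full protocol.

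Much of this stands. Missing adjudication detail is no finding in a condensed article, and emergency access needs no change. The exception itself does not contradict Study Design. But the request sentence is a stated instruction, not an omission. It carries no emergency condition and names the fellow apart from the treating personnel. A fellow who both treats and records gives more reason to protect the record.

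A reader might go further and infer that complications in general are classified with the arm known, or that the safety comparison is biased by a relative risk such as 1.6. The document supports neither. Apart from suspected renal failure, unblinding is only permitted; several monitoring tasks belong to other staff; and the ratio is simply the assumed retention shares divided by each other. The mechanism sets active drug against saline and gives no evident reason for bias between TXA and EACA. Intra-operative blood loss is normally measured before post-operative events arise.

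**Conclusion.** The point holds in a limited form. The release-on-request instruction is wider than the emergency condition set for the researcher in the same section, and it undercuts the statement that the researcher is blinded. Complications can be classified with the arm known, and for suspected renal failure they probably will be.

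This rests on two assumptions: that research fellows are among the researchers who complete the data sheets, and that the full protocol has no separate blinded classification. The direction and size of any bias cannot be derived from the document. The change is still worth making, because it is cheap and protects a named outcome.

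**What to change.** - Reconcile the release conditions in Physician Blinding, Adverse events management and Study Design so that they agree. The sponsor should settle how the mandatory renal clause fits with the permissive rules; no clinical unblinding rule is proposed here. Treating staff's emergency access stays as it is.
- End release on bare request to anyone acting as an outcome recorder.
- Handle the researchers' sealed copy of the allocation list (Medication Supply and Randomization) in the same way. Otherwise a limit at the pharmacy leaves the code within their reach.
- Log the time, requester and reason of each release.
- Enter the suspected event and its supporting results on the data sheet before the code is known, where patient care allows.
- Flag events classified after unblinding and report them separately.

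The cost is some protocol wording, a revised pharmacy instruction and a log. The small downside is that the event entry has to be made without the code.
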